#### Analysis

Statistical and social network analysis will be used to characterise and describe the results, using multiple imputation of missing data prior to analysis [55,81]. In examining the association between various social factors, data will be aggregated and entered in SPSS, UCINET, NetDraw and Microsoft Excel for statistical and network analysis. In assessing if tobacco control programs have influenced behaviours, attitudes and beliefs in relation to smoking, analysis will incorporate common descriptive statistics and comparisons between the pre- and post-intervention groups. For example, comparisons between the pre and post-intervention groups will use X^2^ (categorical distributions) and T-tests (interval or ratio data). Bivariate associations between variables will be tested by X^2^ in analysing smoking type (daily smoker, occasional smoker, light smoker, social smoker, ex-smoker and non-smoker) by gender, age group, income group, education level, etc. Wilcoxon rank sum tests or Spearmans rank correlations will also be used depending on whether the variables are binary or ordinal. Multiple regression will be used to test whether individual variables are independently predictive of outcomes. Comparisons will be conducted across and between the sub-groups for both pre- and post-intervention [81,99]. Analysis will also include examining the data from the Fagerström Test for Nicotine Dependence questions in the survey for reductions in means scores, indicating reduced nicotine dependence. The higher the accumulated Fagerström score per participant, the more intense the participant’s physical dependence on nicotine [84]. Computations will be undertaken using SPSS and Microsoft Excel [83-85].

Social network analysis will be used to assess if individuals' social networks influence smoking behaviours. Network analysis will include exploring smoking and non-smoking networks constructed from the survey data and complemented by the qualitative data collection. This will include network visualization, structural analysis and statistical analysis [55]. Several network level measures of structure will be assessed, including clustering, network size, number of ties and reciprocity [55,58]. To study the clustering of smoking behaviour, we will compare the observed network at each data collection point to a simulated network with the same network characteristics, including the same overall rate of smoking prevalence, but with the incidence of smoking randomly distributed across the network [59]. If clustering is occurring among smokers or non-smokers, the probability that a participant who smokes has contact with other smokers should be higher in the observed network than in the simulated network [21,60]. These network metrics will be used to provide a descriptive presentation of the network/s and any changes over time. The pre- and post-test survey will be analysed using Analysis of Variance (ANOVA) on the gain scores and Analysis of Covariance (ANCOVA).

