**Methods and design:**

Our prospective study will use a mixed-method approach (qualitative and quantitative), including a pre- and post-test evaluation of a tobacco control initiative. The study will explore the social and cultural context underlying Indigenous Australian tobacco use and associated factors which influence smoking behaviour. Primary data will be collected via a panel survey, interviews and focus groups. Secondary data will include de-identified PBS items related to smoking and also data collected from the Quitlines call service. Network analysis will be used to assess whether social networks influence smoking behaviours. For the survey, baseline differences will be tested using chi^2^ statistics for the categorical and dichotomous variables and t-tests for the continuous variables, where appropriate. Grounded theory will be used to analyse the interviews and focus groups. Local Aboriginal community controlled organisations will partner in the study.

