## Methods/design

### Aim and objectives

The objectives of the research are to answer the following questions:

•do individuals' social networks influence smoking behaviours;

•is there an association between various social and cultural factors and being a smoker or non-smoker; and

•do the tobacco control programs under the Action Area 1 of the ACT Aboriginal and Torres Strait Islander Tobacco Control Strategy 2010–2014 (this includes smoking cessation groups, youth and community health promotion programs and education campaigns) impact on tobacco behaviours, attitudes and beliefs in the Indigenous Australian population.

We will undertake surveys, focus groups and interviews in two waves approximately 12 months apart; pre- and post-implementation of the multi-component tobacco control initiative. This will assist to identify commonalities and disparities, assessing the effectiveness of program and further exploring socio-environmental mechanisms that influence tobacco use, attitudes and behaviours [81,82]. Data will be collected via:

1. surveys;

2. interviews;

3. focus groups; and

4. use of existing de-identified health data, for example, the Talking About the Smokes survey data, data regarding relevant Pharmaceutical Benefit Scheme (PBS) item listings related to smoking (e.g. item codes for nicotine replacements) and Quitlines call data and volume.

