#### Sample size

A minimum sample size of 102 participants was determined. This sample size is sufficient to obtain 90 per cent power to detect a 10 per cent reduction in smoking between the pre-intervention group (36%) when compared with the post-intervention group. The current population smoking rate is based on data obtained from the 2008 National Aboriginal and Torres Strait Islander Social Survey (NATSISS) relating to the ACT Indigenous Australian population [87].

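### The protocol leaves open whether the two survey waves are linked, and the only pre/post test it names for smoking status, a chi-square, ignores the pairing if they are

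*Protocol article*

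**What the plan says.** Some places point to linked waves:

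- Abstract, Methods and design: "Primary data will be collected via a panel survey, interviews and focus groups".
- The survey, Analysis, closing sentence: "The pre- and post-test survey will be analysed using Analysis of Variance (ANOVA) on the gain scores and Analysis of Covariance (ANCOVA". A gain score is one person's second value minus their first, and ANCOVA in this setting adjusts for the person's own baseline. Neither can be computed without linkage.

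Other places point to two separate samples:

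- The survey, Sample size: the reduction is measured from the "pre-intervention group (36%) when compared with the post-intervention group".
- The survey, Analysis, first paragraph: "comparisons between the pre and post-intervention groups will use X^2^ (categorical distributions) and T-tests (interval or ratio data".

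The Aim and objectives section fixes the timing, "in two waves approximately 12 months apart; pre- and post-implementation of the multi-component tobacco control initiative", but does not say that the same people answer both times.

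The size of the study rests on smoking status: "A minimum sample size of 102 participants was determined", said to be "sufficient to obtain 90 per cent power to detect a 10 per cent reduction in smoking". The text does not say whether 102 means people in total, people per wave, or pairs followed to the second wave. It names no paired test for smoking status.

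**The concern.** The third research question asks whether the tobacco control programs change behaviour, and smoking status is the outcome used to size the study. Either way of reading the design leaves something in the plan to change:

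- **Waves linked.** An ordinary chi-square treats one person's two answers as coming from two unrelated people. Smoking status 12 months apart is likely to be positively correlated within a person. The test then overstates the standard error of the change and discards information that the design paid for.
- **Waves not linked.** The chi-square is appropriate, but the gain-score and own-baseline ANCOVA analyses cannot be done, and the survey is not a panel.

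What is at stake is mainly a missed effect. There is also a practical risk: waves collected without an identifier may not be linkable afterwards.

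**Working it through.** **Inputs from the protocol article (The survey, Sample size).** Baseline p1 = 0.36; n = 102; target power 90%; a 10 per cent reduction, read here as 10 percentage points, so p2 = 0.26.

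**Assumptions.** Two-sided alpha of 0.05. Within-person correlation rho of 0.3, 0.5 and 0.7, shown as a range because the document gives none.

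**1. The plan's own figure.** For two independent groups with a pooled variance under the null:

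n per group = [1.96 × √(2 × 0.31 × 0.69) + 1.2816 × √(0.36 × 0.64 + 0.26 × 0.74)]² / 0.10²
= [1.96 × 0.6541 + 1.2816 × 0.6502]² / 0.01 ≈ 448.

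One-sided it is 365. The relative reading (36% to 32.4%) needs 3,647 per group. None of these gives 102. Two special readings come close:

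- McNemar's test with all change in one direction (10% stop, nobody starts) needs 101 pairs.
- A fall *to* 10%, one-sided with continuity correction, needs 51 per group, or 102 in total.

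The document states neither.

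**2. If the waves are independent, 102 per wave.** The chi-square needs an observed difference of at least 1.96 × 0.6541 / √102 = 0.127. The standard error is √((0.2304 + 0.1924)/102) = 0.064. Power = Φ((0.10 − 0.127)/0.064) ≈ 34%. With 51 per wave it is 19%.

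**3. If the same 102 people are linked.**

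- Proportion smoking at both waves: p11 = p1·p2 + rho × √(0.2304 × 0.1924) = 0.0936 + 0.2105 × rho.
- Discordant proportion: pd = 0.36 + 0.26 − 2·p11.
- Paired standard error: √((pd − 0.10²)/102).
- McNemar power: Φ((0.10 × √102 − 1.96 × √pd)/√(pd − 0.01)).
- Power of the ordinary chi-square on the same pairs: Φ((0.10 − 0.127)/paired standard error).
- True type I error of the ordinary chi-square: 2 × (1 − Φ(1.96/√(1 − rho))).
- Pairs for 90% power by McNemar: [1.96 × √pd + 1.2816 × √(pd − 0.01)]² / 0.01.

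| rho | pd | Unpaired SE | Paired SE | Power, chi-square | Power, McNemar | Type I error, chi-square | Pairs for 90% (McNemar) |
|---|---|---|---|---|---|---|---|
| 0.3 | 0.306 | 0.064 | 0.054 | 31% | 45% | 1.9% | 318 |
| 0.5 | 0.222 | 0.064 | 0.046 | 28% | 57% | 0.6% | 230 |
| 0.7 | 0.138 | 0.064 | 0.035 | 22% | 78% | 0.03% | 141 |

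The largest correlation compatible with 36% and 26% is 0.79. There pd = 0.10, nobody starts smoking, and McNemar with 102 pairs has 90% power. The chi-square loses power as rho rises because its threshold of 0.127 stays above the true change of 0.10 while the observed change becomes less variable.

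**The case against.** The strongest reply is that the document never says the tests are for independent samples. It offers chi-square and t-tests as an example. A t-test can be paired, McNemar's test is itself a chi-square test, and a condensed article may leave the variant to the analysis plan. That stands for the t-tests. It stands less well for smoking status, where an unqualified chi-square between pre and post groups would ordinarily be read as the unpaired test, and the sample size uses the same two-group framing.

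Second, same-person follow-up is itself an inference, from the word panel and from the gain scores. That also stands. It is why the point is a need to reconcile the sections, and not a finding that the error bars are wrong.

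Third, a linked analysis is already planned. For score outcomes such as the Fagerström mean, gain scores and ANCOVA use the pairing. A reader might infer that the whole pre/post comparison loses most of its power, or that the two sets of analyses cannot coexist. The documents do not support either: chi-square for categorical outcomes and gain scores for scale outcomes can sit side by side once linkage is settled. The gap is confined to smoking status.

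Fourth, pairing alone does not rescue the stated 90%, because McNemar's test falls short over most of the range. That is correct, and it is why the sample size statement has to be redone along with the test.

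A reader might also suspect that smoking uptake among participants aged 12 and over distorts the net change. The document gives neither the share of young people nor an uptake rate, and it already plans analyses by age group, so that is not part of this point.

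**Conclusion.** The concern holds for smoking status and is conditional on linkage. If the waves are linked, the ordinary chi-square overstates the standard error by a factor of about 1.2 (0.064/0.054) at a correlation of 0.3, rising to about 1.8 (0.064/0.035) at 0.7. The relative loss of power against McNemar's test is about 31%, 52% and 71% at correlations of 0.3, 0.5 and 0.7. To say that most of the power is lost is therefore fair only from a correlation of about 0.5 upwards, and the document does not supply that figure. The error is conservative: it makes a real reduction easier to miss and does not create a false program effect.

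Under neither reading does 102 deliver 90% power for a 10-point fall as the text stands, apart from the limiting paired case in which essentially nobody starts smoking. These results rest on the absolute reading of the reduction, a two-sided 0.05 level, and 102 taken as complete pairs or as the number per wave.

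**What to change.** State in the Abstract, the Sample size section and the survey Analysis section whether the same people are surveyed and linked at both waves, and make the wording agree.

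**If they are linked:**

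- Put a study ID on the paper and online forms at both waves.
- Replace the chi-square for pre/post smoking status with McNemar's test, or with a GEE or mixed logistic model that has wave as a within-person effect. The model also keeps people who answer only one wave.
- Specify paired tests for scores.
- Restate the power of 102 for complete pairs, giving the assumed proportions who stop and who start smoking.

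**If they are not linked:**

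- Remove the gain-score and own-baseline ANCOVA analyses and the description of the survey as a panel.
- Restate the power for independent groups.

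The cost is wording in three places, an ID field on the forms before the first wave, and one repeated sample size calculation. The larger cost comes only if that calculation leads to a bigger sample.

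### The question about being a smoker or non-smoker is paired with a chi-square on six smoking types that overlap as labelled, giving sparse tables and, for a plain smoker/non-smoker association, a moderate loss of power

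*Protocol article*

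**What the plan says.** In the protocol article, Aim and objectives puts the second question as a two-way contrast: "is there an association between various social and cultural factors and being a smoker or non-smoker". The Research questions section asks the same.

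Under The survey, Analysis, the test named for social factors is: "Bivariate associations between variables will be tested by X^2^ in analysing smoking type". The types and factors are listed as "smoking type (daily smoker, occasional smoker, light smoker, social smoker, ex-smoker and non-smoker) by gender, age group, income group, education level, etc". The section then adds "Wilcoxon rank sum tests or Spearmans rank correlations will also be used depending on whether the variables are binary or ordinal" and "Multiple regression will be used to test whether individual variables are independently predictive of outcomes". It does not define the types, reduce them to two levels or say how sparse cells would be handled.

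Under The survey, Sample size: "A minimum sample size of 102 participants was determined", with smoking at 36% before the intervention. That number was set for the change in smoking between waves. No power is claimed for the social-factor question.

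**The concern.** A contingency table needs rows that exclude each other. These labels mix frequency (daily, occasional), quantity (light), setting (social) and history (ex-smoker). As worded, a light smoker can smoke daily, a social smoker can be an occasional one, and an ex-smoker is at present a non-smoker. A question with two outcomes is thus matched to a test with six, and the boundary between the two outcomes is left open exactly where ex-smokers sit.

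Two things are at stake. The answer to the second question can change with where ex-smokers are placed. And spreading a two-way contrast over six rows uses up degrees of freedom and leaves few people per cell, so a real difference between smokers and non-smokers is easier to miss.

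**Working it through.** **Plan's own figure.** There is none to reproduce, since the article states no power for this question. How 102 was reached is a separate matter; it is used here only as the stated minimum.

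**Inputs from the article.** n = 102; smoking 36%; six types. **Assumed, because not stated:** two-sided alpha 0.05; groups of equal size on average; 2 to 5 levels per social factor; smokers split over the four smoker types either 60/15/15/10% or equally; 35% of non-smokers are ex-smokers. Whether 102 is per wave or in total is also not stated.

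**1. Sparseness.** Smokers: 0.36 × 102 = 36.7. For a factor with k levels, the average expected count is 102/(6k) over all cells and 36.7/(4k) in the four smoker rows.

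| Levels k | All cells | Smoker rows |
|---|---|---|
| 2 | 8.5 | 4.6 |
| 3 | 5.7 | 3.1 |
| 4 | 4.25 | 2.3 |
| 5 | 3.4 | 1.8 |

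In simulation (8,000 tables per setting), the share of expected counts below 5 was about 48% (60/15/15/10 split) and 41% (equal split) for 6×2 tables, and 62% and 72% for 6×4 tables. With two smoking rows it was under 0.5%. With no association, the six-type test rejected about 4% of the time, so it is slightly conservative, not inflated.

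**2. Power when the association lies wholly between smokers and non-smokers.** The noncentrality is λ = n·w², where w is Cohen's effect size. It is the same for both tables; only the degrees of freedom differ: k − 1 for two rows, 5(k − 1) for six. Power is the chance that a noncentral chi-square with that λ exceeds the 5% critical value.

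Example with k = 2: w = 0.277 gives λ = 102 × 0.277² ≈ 7.8. Power is 80% on 1 df and 56% on 5 df.

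| Levels k | df, two rows / six rows | Six-type power when binary is 80% | Six-type power when binary is 90% |
|---|---|---|---|
| 2 | 1 / 5 | 56% | 70% |
| 3 | 2 / 10 | 52% | 67% |
| 4 | 3 / 15 | 50% | 65% |
| 5 | 4 / 20 | 49% | 63% |

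Relative loss for k = 2: (80 − 55.5)/80 = 31% and (90 − 70.3)/90 = 22%. For k = 5: (80 − 48.6)/80 = 39% and (90 − 62.6)/90 = 30%.

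**3. Simulation at n = 102.** For two equal groups averaging 36%, w = (difference/2)/√(0.36 × 0.64) = (difference/2)/0.48.

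- 22.5% v 49.5% (w = 0.135/0.48 = 0.28): binary 82%, six-type 56%.
- 26% v 46% (w = 0.10/0.48 = 0.21): binary 56%, six-type 30%.
- Four groups at 15/35/45/49% (mean 36%): binary about 66%, six-type about 31%.

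Changing the type split hardly moved these results.

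**4. When the association lies elsewhere.** In a scenario where the groups differed mainly in ex- versus never-smoking, the order reversed: binary 19%, six-type 60%.

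**The case against.** The strongest reply is that much of this is inferred. The questionnaire item is not shown. A single-choice item would give exclusive categories, and listing ex-smoker beside non-smoker suggests that non-smoker there means never-smoker. That may be so, but the article does not say it, and the side on which ex-smokers fall would still be open.

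Second, a reader might infer that the six-type table is the only test of this question. The article does not support that. The same section plans rank tests and regression, its network analysis compares smokers with non-smokers, the sample size rests on a two-way smoking rate, and nothing rules out a binary comparison. What stands is that the one bivariate method spelled out for smoking against gender, age, income and education does not match the question.

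Third, a reader might infer that power is roughly halved in general. It is not. The loss nears half only where the binary test is itself weak, at about 50–65% power or lower (50% to 28% for two levels; about 66% to 31% in the four-group example). The sample starts at age 12, so ex-smoking may well differ by age, and then the six-type test can win.

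Fourth, a reader might infer that a linear model will be fitted to a yes/no outcome, or that 37 smokers allow only a handful of predictors. The article gives neither the form of the regression nor the number of predictors, its outcomes also include the Fagerström score, and any limit per predictor is an outside rule of thumb. Neither point carries weight here.

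Lastly, sparse cells are not shown to inflate false positives, and rules for collapsing cells are ordinary analysis-plan detail. Both are accepted.

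**Conclusion.** The point holds as a mismatch between question and stated method. The question has two outcomes, the named chi-square has six that overlap as labelled, and the place of ex-smokers is not fixed. That part needs no assumptions.

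The size is conditional. With 102 participants and 36% smoking, the tables are sparse under either assumed type split. If the association is purely between smokers and non-smokers, power falls by 20 to 31 percentage points from a starting level of 80–90%, or about 22–39% in relative terms. This rests on a 5% two-sided level, 2 to 5 factor levels, and no association within smoker types or between ex- and never-smokers. It is a loss of sensitivity and clarity, not a threat to the type I error rate. It is worth correcting because the correction is cheap.

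**What to change.** In The survey, Analysis:

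- Make current smoker yes/no the main outcome for the second research question, with ex-smokers counted as non-smokers.
- Add mutually exclusive current/ex/never categories as a secondary outcome. This covers the case where groups differ in quitting rather than in current smoking.
- Use chi-square or exact tests on these outcomes, and name logistic regression where the outcome is smoking status.
- Keep the six types for description.

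The cost is wording only, provided that current, former and never smoking can be derived from the survey answers. The downside is that differences among the finer smoking types are described and not tested.

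### A fall in mean Fagerström score is read as reduced dependence without fixing whose scores are averaged; if the smokers differ between waves, the mean can move with no individual change

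*Protocol article*

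**What the plan says.** All references are to the Protocol article.

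- **The survey, Analysis, first paragraph.** Fagerström data are to be examined "for reductions in means scores, indicating reduced nicotine dependence". The next sentence gives the meaning of the score for an individual: "The higher the accumulated Fagerström score per participant", the stronger the physical dependence. The same paragraph says that "comparisons between the pre and post-intervention groups will use" chi-square tests for categorical data and t-tests for interval or ratio data. It also plans multiple imputation of missing data before analysis, with no exception stated.
- **Same paragraph, smoking types.** Respondents are classed as "daily smoker, occasional smoker, light smoker, social smoker, ex-smoker and non-smoker", so the survey is not confined to smokers.
- **The survey, Analysis, second paragraph.** "The pre- and post-test survey will be analysed using Analysis of Variance (ANOVA) on the gain scores and Analysis of Covariance (ANCOVA").
- **Abstract, Methods and design.** "Primary data will be collected via a panel survey, interviews and focus groups".
- **Aim and objectives.** Data are collected "in two waves approximately 12 months apart", before and after the programme.
- **The survey, Sample size.** The minimum of 102 is meant to detect a 10 per cent "reduction in smoking between the pre-intervention group (36%) when compared with the post-intervention group".
- **The sample population.** People aged 12 and above are included, partly because tobacco use starts early.

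No passage says whether the Fagerström mean covers current smokers at each wave, all respondents with non-smokers at zero, or people smoking at both waves.

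**The concern.** The score is described for an individual, but the inference is drawn from a group mean. That step is safe only if the same people are averaged both times. Here the set of smokers is likely to change: the programme aims for fewer smokers, the waves are about a year apart, and the sample reaches down to ages at which people start to smoke.

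If each wave's mean is taken over that wave's smokers, people who quit drop out of the second mean and people who start come into it. The mean can then fall although nobody became less dependent, or rise although the programme worked by helping the less dependent to stop. The plan's rule would credit the first as reduced dependence and find none in the second. The result feeds the research question on programme impact, although it is not the outcome behind the sample size.

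**Working it through.** The article gives no Fagerström mean, standard deviation or target difference, so there is no figure of the plan's own to reproduce. The calculation below illustrates how far composition alone can move the mean.

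**Inputs**
- From Sample size: 102 participants, 36% smoking before the programme, 10 per cent reduction. The article does not say whether 102 is a total or per wave; I take 102 people followed through both waves.
- Wave-1 smokers: 0.36 × 102 = 36.7, about 37.
- Absolute reading of the reduction (36% to 26%): 0.26 × 102 = 26.5, about 27 smokers, so 10 quitters.
- Relative reading (36% to 32.4%): 0.324 × 102 = 33.0, so 33 smokers and 4 quitters.
- Assumed, not in the article: baseline mean among smokers 4.0 (score total 37 × 4.0 = 148); quitters' baseline mean 2 to 6; new smokers score 1; no continuing smoker's score changes.

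**Quitting only, mean over each wave's smokers**

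Wave-2 mean = (148 − q × m) / (37 − q), where q is the number of quitters and m their baseline mean.

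| Quitters | m | Wave-2 mean | Change |
|---|---|---|---|
| 10 | 2 | 128/27 = 4.74 | +0.74 |
| 10 | 3 | 118/27 = 4.37 | +0.37 |
| 10 | 4 | 108/27 = 4.00 | 0.00 |
| 10 | 5 | 98/27 = 3.63 | −0.37 |
| 10 | 6 | 88/27 = 3.26 | −0.74 |
| 4 | 2 | 140/33 = 4.24 | +0.24 |
| 4 | 3 | 136/33 = 4.12 | +0.12 |

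The sign depends on whether quitters were below or above the average.

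**Uptake only, no quitting**

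Wave-2 mean = (148 + e × 1) / (37 + e), where e is the number of new smokers.
- e = 3: 151/40 = 3.775
- e = 5: 153/42 = 3.64
- e = 8: 156/45 = 3.47

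**Both together, 10 quitters**
- m = 6, e = 3: (148 − 60 + 3)/30 = 3.03; e = 5: (148 − 60 + 5)/32 = 2.91
- m = 2, e = 3: (148 − 20 + 3)/30 = 4.37; e = 5: (148 − 20 + 5)/32 = 4.16

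Across these scenarios the smoker mean moves by between −1.09 (2.91 − 4.0) and +0.74.

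**Alternative populations**
- All 102, non-smokers at 0, 10 quitters, no uptake: change = −10 × m/102, from −20/102 = −0.20 (m = 2) to −60/102 = −0.59 (m = 6). This always falls, and the whole fall is quitting.
- Only people smoking at both waves: change = 0 in every scenario, as it should be when no individual changed.

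**The case against.** The strongest reply is that the article never says the mean is over current smokers. If non-smokers count as zero, quitters stay in the average, it falls when people quit, and the rule points the right way. This stands as far as it goes: the artefact depends on an averaging choice that the article leaves open. But a fall under that choice restates the drop in smoking and does not show that continuing smokers became less dependent.

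The second reply is that the survey is a panel with gain scores and ANCOVA planned. If non-smokers have no score, gain scores exist only for people smoking at both waves, which removes the artefact. This also partly stands. However, that sentence concerns the survey in general and does not replace the Fagerström rule, which sits beside comparisons of groups. Nor does the article say what score a quitter has at wave 2 or a new smoker at wave 1. With imputation planned without exception, an inapplicable score could be filled in as though the person still smoked.

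Third, a condensed article may leave the averaged population to a fuller document. That would settle a mere omission. Here the article itself fixes an interpretation without qualification.

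A reader might go further and infer that the rule is simply wrong, or that programme success will appear as higher dependence. The article does not support either. The direction turns on who quits, and quitters near the average leave the mean unchanged. Nor does the sample-size statement forecast that 10 points of the panel will quit: it names a detectable effect and does not say whether it is absolute or relative.

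**Conclusion.** The point holds in a limited form. A lower mean Fagerström score can mislead as a sign of reduced dependence, because the article does not fix whose scores are averaged and the set of smokers can change between waves. Composition alone can plausibly shift a smoker-only mean by some tenths of a point, up to about one point in the most extreme scenario tried, in either direction.

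Those sizes rest on an assumed baseline mean of 4.0, assumed scores for quitters and new smokers, 102 people followed at both waves, and a mean taken over each wave's smokers. They show what is possible and do not predict the result. A comparison restricted to the same continuing smokers removes the artefact, and the planned panel and gain scores go part of the way there. The analysis is supplementary and smoking status is assessed separately, so this is a cheap improvement of modest severity.

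**What to change.** In the survey Analysis section, replace the sentence on mean Fagerström scores with a rule that:

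1. defines the analysis as within-person change among people smoking at wave 1;
2. reads a fall as reduced dependence only in those smoking at both waves, reported next to the number who quit;
3. adds a second version in all wave-1 smokers with quitters scored 0;
4. states that a quitter's wave-2 score is not missing and is not imputed as if the person still smoked;
5. reports the scores of new smokers separately, with their number.

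The sentence on gain scores and ANCOVA should say that it applies to the Fagerström score in this form.

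The cost is wording only, given the linked records that a panel with gain scores already implies. There are two drawbacks: scoring quitters as 0 is a convention, and the continuing-smoker set is small (about 27 to 33 people in the illustration, before any dropout). That is why both versions should be shown.
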